APPENDIX B SCHEDULE OF PROCEDURES/EVALUATIONS (continued)

|                                                   |                           | Month      | 6 (4)            |     |     |                |                |       | 7 (5) | 8 (6)  | 9 (7) | 10 (8)  | 11(9)  | 12    | 24  |
|---------------------------------------------------|---------------------------|------------|------------------|-----|-----|----------------|----------------|-------|-------|--------------------|-------|---------------------|--------------------|-------|-----------------|
|                                                   |                           | Day (US)   | 180  |     |     | 183            | 187            | 194   | 210   |                    | 270   |                     |                    | 360   | 720             |
| Procedures                                        | Blood Volume  | Day (Mali) | 120  | 121 | 122 | 123            | 127            | 134   | 150   | 180                | 210   | 240                 | 270                | 360   | 720             |
| Complete History/Physical                         |                           |            |                  |     |     |                |                |       |       |                    |       |                     |                    |       |                 |
| Obtain Informed Consent                           |                           |            |                  |     |     |                |                |       |       |                    |       |                     |                    |       |                 |
| Interim Clinical Evaluation                       |                           |            | X                | X   | X   | X              | X              | X     | X     | X                  | X     | X                   | X                  | X     | X               |
| CBC                                 | 5 mL                      |            | X                |     |     | X              | X              | X     |       |                    |       |                     |                    |       |                 |
| ALT/Creatinine                                    | 5 mL                      |            | X                |     |     | X              | X  | X     |       |                    |       |                     |                    |       |                 |
| Urine dipstick                                    |                           |            | X                |     |     | X  | X              | X     | X     |                    | X     |                     |                    | X     |                 |
| Urine pregnancy test (females)                    |                           |            | X                |     |     |                |                | X     |       |                    |       |                     |                    |       |                 |
| Urine for chloroquine and metabolites (Mali)      |                           |            | X                |     |     |                |                |       |       |                    |       |                     |                    |       |                 |
| HIV (US)                                          | 5 mL                      |            |                  |     |     |                |                |       |       |                    |       |                     |                    |       |                 |
| HbsAg & HCV ELISA (US)                            | 5 mL                      |            |                  |     |     |                |                |       |       |                    |       |                     |                    |       |                 |
| Anti-dsDNA                                        |                           |            |                  |     |     |                |                | X     |       |                    |       |                     |                    | X     |                 |
| Hepatitis B and C dipstick (Mali)                 |                           |            |                  |     |     |                |                |       |       |                    |       |                     |                    |       |                 |
| Baseline stored serum                 | 5 mL                      |            |                  |     |     |                |                |       |       |                    |       |                     |                    |       |                 |
| VACCINATION                                |                           |            | X                |     |     |                |                |       |       |                    |       |                     |                    |       |                 |
| Anti-AMA1/MSP1 antibody ELISA                     | 5 mL                      |            | X                |     |     |                |                | X     |       |                    | X     |                     |                    | X     |                 |
| B cell analysis                                   | 20 mL                     |            | X                |     |     |                | X              |       |       |                    |       |                     |                    | X     |                 |
| GIA and/or T cell studies             | 20 mL                     |            |                  |     |     |                | X              | X     |       |                    |       |                     |                    | X     |                 |
| Malaria smears and filter paper collection (Mali) |                           |            | X                |     |     |                |                | X     | X     | X                  | X     | X                   | X                  | X     |                 |
| Blood Volume in mL                         |                           |            | 35               |     |     | 10             | 50             | 40    |       |                    | 5     |                     |                    | 50    |                 |
| Mali (US)                      |                           |            | (40)             |     |     |                |                |       |       |                    |       |                     |                    |       |                 |
| Total Blood Volume in mL                   |                           |            | 280              |     |     | 290            | 340            | 380   |       |                    | 385   |                     |                    | 435   |                 |
| Mali (US)                                  |                           |            | (275)            |     |     | (285)          | (330)          | (370) |       |                    | (375) |                     |                    | (425) |                 |

 These procedures/ visits will occur in Mali only.

This visit is optional in the US

## APPENDIX C: TOXICITY TABLE

| Local Adverse Event          | Grade | Intensity                                                                     |
|------------------------------|-------|-------------------------------------------------------------------------------|
| Pain at injection site       | 1     | Pain that is easily tolerated                                                 |
|                              | 2     | Pain that interferes with daily activity or treatment given                   |
|                              | 3     | Pain that prevents daily activity                                             |
| Erythema at injection site   | 1     | >0 mm - ≤20 mm                                                                |
|                              | 2     | >20 mm - ≤50 mm                                                               |
|                              | 3     | >50 mm                                                                        |
| Swelling at injection site   | 1     | >0 mm - ≤20 mm                                                                |
|                              | 2     | >20 mm - ≤50 mm                                                               |
|                              | 3     | >50 mm                                                                        |
| Induration at injection site | 1     | >0 mm - ≤20 mm                                                                |
|                              | 2     | >20 mm - ≤50 mm                                                               |
|                              | 3     | >50 mm                                                                        |
| Solicited Adverse Event      | Grade | Intensity                                                                     |
| Fever (oral)                 | 1     | 100.4°F – 101.5°F (38.0°C – 38.6°C)                                           |
|                              | 2     | 101.6°F – 102.4°F (38.7°C – 39.1°C)                                           |
|                              | 3     | ≥102.5°F (≥39.2°C)                                                            |
| Headache                     | 1     | Headache that is easily tolerated                                             |
|                              | 2     | Headache that interferes with daily activity, or treatment given              |
|                              | 3     | Headache that prevents daily activity                                         |
| Nausea                       | 1     | Nausea that is easily tolerated                                               |
|                              | 2     | Nausea that interferes with daily activity, or treatment given                |
|                              | 3     | Nausea that prevents daily activity                                           |
| Malaise                      | 1     | Malaise that is easily tolerated                                              |
|                              | 2     | Malaise that interferes with daily activity, or treatment given               |
|                              | 3     | Malaise that prevents daily activity                                          |
| Myalgia                      | 1     | Myalgia that is easily tolerated                                              |
|                              | 2     | Myalgia that interferes with daily activity, or treatment given               |
|                              | 3     | Myalgia that prevents daily activity                                          |
| Arthralgia                   | 1     | Arthralgia that is easily tolerated                                           |
|                              | 2     | Arthralgia that interferes with daily activity, or treatment given            |
|                              | 3     | Arthralgia that prevents daily activity                                       |
| Urticaria                    | 1     | Requiring no medications                                                      |
|                              | 2     | Requiring PO or topical treatment or IV medications or steroids for ≤24 hours |
|                              | 3     | Requiring IV medication or steroids for >24 hours                             |

## APPENDIX D: TOXICITY TABLE FOR GRADING LABORATORY ADVERSE EVENTS

### US

| Laboratory Test                                              | Grade 1                      | Grade 2                     | Grade 3                                               | Grade 4 (Life threatening)             |
|--------------------------------------------------------------|------------------------------|-----------------------------|-------------------------------------------------------|----------------------------------------|
| Hgb (female) – decrease from testing laboratory LLN in gm/dl | 1.0 - <1.5                   | ≥1.5 & <2.0                 | ≥2.0                                                  | Requires transfusion                   |
| Hgb (male) – decrease from testing laboratory LLN in gm/dl   | ≥1.5 & <2.0                  | ≥2.0 & <2.5                 | ≥2.5                                                  | Requires transfusion                   |
| Absolute neutrophil count (ANC, cells/mm  )      | 1000-1499                    | 500-999                     | <500                                                  | <500 with fever                        |
| Leukopenia (WBC, cells/mm  )                     | <3500 - ≥2500                | <2500 - ≥1500               | <1500                                                 | <1500 with fever                       |
| Platelets (cells/mm  )                           | 125,000 – 135,000            | 100,000 – 124,000           | 20,000-99,000                                         | <20,000                                |
| ALT                                                          | 1.25 – 2.5 x ULN             | 2.6 – 5.0 x ULN             | >5.0 x ULN                                            | >10 x ULN and requires hospitalization |
| Creatinine                                                   | 1.1 – 1.5 x ULN              | 1.6 – 3.0 x ULN             | >3.0 x ULN                                            | >5.0 x ULN and requires dialysis       |
| Urine protein                                                | 2+ or 0.5-1 gm loss/day      | 3+ or 1-2 gm loss/day       | 4+ or >2 gm loss/day                                  | NA                                     |
| Hematuria                                                    | 2+ confirmed by 5-10 rbc/hpf | 3+ confirmed by >10 rbc/hpf | gross, with or without clots, OR red blood cell casts | NA                                     |

### Mali

| Laboratory Test                | Grade 1 (Mild)                    | Grade 2 (Moderate)                | Grade 3 (Severe)                                      | Grade 4 (Life threatening)             |
|--------------------------------|-----------------------------------|-----------------------------------|-------------------------------------------------------|----------------------------------------|
| Hemoglobin
Males
Females | 8.5 – 9.5 g/dL
7.0 – 8.0 g/dL  | 7.5 – 8.4 g/dL
6.0 – 6.9 g/dL  | <7.5 g/dL
<6.0 g/dL                                | Requires transfusion                   |
| Platelets                      | 75,000 - 99,999/mm    | 50,000 - 74,999/mm    | 20,000 – 49,999/mm                        | <20,000/ mm                |
| WBCs (Increase)                | ≥11,500 – 15,000/ mm  | >15,000 - 20,000 /mm  | >20,000/mm                                | NA                                     |
| WBCs (Decrease)                | <3500-2500/ mm        | <2500-1000/ mm        | <1,000 / mm                               | <1,000/ mm  with fever     |
| Absolute Neutrophil Count      | 1000 -1500/mm         | 500-999/mm            | <500/mm                                   | <500/mm  with fever        |
| Absolute Granulocyte Count     |                                   |                                   |                                                       |                                        |
| Creatinine                     | 1.1 - 1.5 x ULN                   | 1.6 - 3.0 x ULN                   | >3.0 x ULN                                            | >5.0 x ULN and requires dialysis       |
| ALT                            | 1.25 - 2.5 x ULN                  | 2.6 - 5 x ULN                     | >5 x ULN                                              | >10 x ULN and requires hospitalization |
| Proteinuria                    | 2+ or 500 mg - 1 gm loss/day      | 3+ or >1- 2 gm loss/day           | 4+ or >2 gm loss/day                                  | NA                                     |
| Hematuria                      | 2+ confirmed by 5-10 rbc/hpf      | 3+ confirmed by >10 rbc/hpf       | gross, with or without clots, OR red blood cell casts | NA                                     |

ULN= upper limits of normal

## APPENDIX E: TABLE FOR GRADING ADVERSE EVENTS

These tables are to be used to grade unexpected adverse events not described in Appendixes C and D.

| Vital Signs*                                                                         | Mild (Grade 1)   | Moderate (Grade 2) | Severe (Grade 3) | Life threatening (Grade 4) |
|---------------------------------------------------------------------------------------------|-------------------------|---------------------------|-------------------------|-----------------------------------|
| Tachycardia – beats per minute                                                              | 110-120                 | 120-140                   | >140                    | >160 with symptoms**              |
| Bradycardia – beats per minute                                                              | 50-54                   | 45-49                     | <45                     | <35 with loss of consciousness    |
| Hypertension (systolic) – mm Hg (with repeat testing at same visit)                         | 141-150                 | 151-170                   | >170                    | >200 with symptoms**              |
| Hypertension (diastolic) – mm Hg (with repeat testing at same visit)                        | 91-100                  | 100-110                   | >110                    | >120 with symptoms**              |
| Hypotension (systolic) – mm Hg (with repeat testing at same visit)                          | 85-89 (and symptomatic) | 80-84 (and symptomatic)   | <80                     | <70 with loss of consciousness    |
| * Subject should be at rest for measurement of vital signs                                  |                         |                           |                         |                                   |
| ** Severe headache, chest pain, altered consciousness, or other signs of acute organ damage |                         |                           |                         |                                   |

| Systemic | Mild (Grade 1)                                                        | Moderate (Grade 2)                                                                    | Severe (Grade 3)                                   | Life Threatening (Grade 4) |
|-----------------|------------------------------------------------------------------------------|----------------------------------------------------------------------------------------------|-----------------------------------------------------------|-----------------------------------|
| Anorexia        | Loss of appetite without decreased oral intake lasting greater than 48 hours | Loss of appetite associated with decreased oral intake without significant weight loss       | Loss of appetite associated with significant weight loss  | NA                                |
| Vomiting        | 1-2 episodes/24 hours                                                        | >2 episodes/24 hours                                                                         | Prevents daily activity, requires outpatient IV hydration | Requires hospitalization          |
| Diarrhea        | 2-3 loose stools/24 hours                                                    | 4-5 loose stools/24 hours                                                                    | >6 loose stools or requires outpatient IV hydration       | Requires hospitalization          |
| Constipation    | NA                                                                           | Persistent constipation requiring regular use of dietary modifications, laxatives, or enemas | Obstipation with manual evacuation indicated              | NA                                |
| Fatigue         | No interference w/activity                                                   | Some interference w/activity                                                                 | Significant, prevents daily activity                      | NA                                |

|                                                             |                                                                                             |                                                                                                                                  |                                                                                                            |                          |
|-------------------------------------------------------------|---------------------------------------------------------------------------------------------|----------------------------------------------------------------------------------------------------------------------------------|------------------------------------------------------------------------------------------------------------|--------------------------|
| Arthritis                                                   | Mild pain with inflammation, erythema or joint swelling – but not interfering with function | Moderate pain with inflammation, erythema or joint swelling – interfering with function, but not with activities of daily living | Severe pain with inflammation, erythema or joint swelling –and interfering with activities of daily living | NA                       |
| Mucocutaneous Reaction/Rash                                 | Erythema; pruritus or localized macular rash                                                | Diffuse, maculo-papular rash, dry desquamation                                                                                   | Vesiculation or moist desquamation or ulceration                                                           | Requires hospitalization |
| Vasovagal episode (associated with a procedure of any kind) | Present without loss of consciousness                                                       | Present with transient loss of consciousness                                                                                     | NA                                                                                                         | NA                       |
| Vertigo                                                     | Causes no or minimal interference with usual daily activities                               | Causes greater than minimal interference with usual daily activities                                                             | Inability to perform daily activities                                                                      | NA                       |
| Cough                                                       | transient- no treatment                                                                     | persistent cough; treatment responsive                                                                                           | Paroxysmal cough; uncontrolled with treatment                                                              | Requires hospitalization |
| Bronchospasm, Acute                                         | transient; no treatment; 70% - 80% FEV 1 of peak flow                            | requires treatment; normalizes with bronchodilator; FEV 1 50% - 70% (of peak flow)                                    | no normalization with bronchodilator; FEV 1 25% - 50% of peak flow; or retractions present      | Requires hospitalization |
| Dyspnea                                                     | Dyspnea on exertion                                                                         | Dyspnea with normal activity                                                                                                     | Dyspnea at rest                                                                                            | Requires hospitalization |

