Engerix-B® mixed with CPG 7909 was also evaluated in a randomized, double-blind controlled trial in 58 HIV-infected adults in Canada [42]. The most common adverse events were local injection site reactions and influenza-like symptoms. Serious adverse events were reported in 2 individuals who received Engerix-B® with CPG 7909: 1 who developed unstable angina and myocardial infarction 2 and 4 months after the last vaccination respectively, and 1 who had laparoscopy for chronic pelvic inflammatory disease 16 days following vaccination. Laboratory abnormalities included transient declines in total lymphocytes and CD4 cells. Two subjects receiving Engerix-B® plus CPG 7909 and 2 subjects receiving CPG 7909 alone had transient elevations of anti-dsDNA; there were no clinical findings of autoimmunity.

The Fluarix® trial was a randomized, controlled, double-blind study in 60 healthy subjects in Canada [40]. Subjects received either the licensed Fluarix® vaccine with or without CPG 7909 or 1/10th the dose of Fluarix® with or without CPG 7909. The most frequently reported adverse events were injection site pain, headache, myalgia, and fatigue. All injection site reactions were mild or moderate in severity, with the exception of 1 volunteer in the 1/10th dose Fluarix® + CPG 7909 group who reported severe pain which resolved without treatment within 4 days. Transient reductions in total white blood cells (WBC), neutrophils, lymphocytes, eosinophils, and platelets were observed in all 4 study arms 2 days post-vaccination, with larger reductions in WBC in the CPG 7909 groups. None of these results were felt to be clinically significant.

CPG 7909 combined with anthrax vaccine absorbed (AVA; licensed as BioThrax®), was evaluated in a randomized, controlled, double-blind study in 69 healthy adults [43]. Local injection site and systemic symptoms were expected and were the most common adverse events. There was a trend to greater frequency and severity of adverse events in the AVA plus CPG 7909 group compared to the AVA alone and CPG 7909 alone groups but this was not statistically significant. Grade 1 leukopenia and hypokalemia were seen in all study arms.

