#### 11.1.1 Primary Objective

The primary objective of this study is to assess safety and reactogenicity of BSAM-2/Alhydrogel®+CPG 7909 in malaria-naïve US adults and semi-immune Malian adults.

- a. The frequency of systemic and local AEs will be summarized.
- b. A line listing of each clinical and laboratory AE classified as local, solicited, or other will be displayed in tables stratified by vaccine allocation and study site.
- c. AEs will be summarized by severity and relationship to vaccine.
- d. The proportion of subjects with at least 1 adverse event will be compared by vaccine and/or dose group within each study site, and tests performed to assess whether these groups differ with respect to these proportions. To see if there is a difference in adverse events between the initial vaccination and the subsequent vaccinations, a sign test will be performed, where the response for each subject is the difference between the numbers of adverse events in the 2 weeks following each vaccination.
- e. SAEs occurring within the study period will be listed by relationship to vaccine.

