#### 12.1.2 Immunization

Possible local vaccine reactions include pain, swelling, erythema, induration, limitation of limb movement for several days, lymphadenopathy, or pruritus at the injection site. Local subcutaneous (SQ) nodules, believed to be granulomatous reactions to aluminum, have been observed with use of aluminum-based adjuvants. Thus, most aluminum-absorbed vaccines are injected intramuscularly (IM) rather than SQ. Systemic reactions such as fever, chills, headache, fatigue, malaise, myalgia, and joint pain may also possibly occur, with some reactions moderate or severe. Immediate hypersensitivity reactions including urticaria, anaphylaxis, or other IgE-mediated responses are possible as with any vaccine. As with any investigational vaccine, there is a theoretical possibility of risks about which we have no present knowledge. Subjects will be informed of any such risks should further data become available.

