Other clinical studies of CPG 7909 used as an adjuvant have shown a moderately increased incidence of mild to moderate local and systemic AEs after vaccination (injection site pain, myalgia, fatigue). Transient lymphopenia, neutropenia, and thrombocytopenia have been seen among patients treated with CPG 7909. These AEs will be monitored and recorded as is standard practice. A Phase 3 clinical study of CPG 7909 in patients with advanced nonsquamous cell lung cancer showed a possible increase in sepsis and thrombocytopenia with bleeding events in subjects receiving CPG 7909. No events such as this have been seen in the studies using CPG

7909 as a vaccine adjuvant described in **Section 1.6**. Subjects with fever are excluded from vaccination and hematologic parameters including platelet counts will be monitored.

With the exception of the Phase 1 study of AMA1-C1/Alhydrogel®+CPG 7909 in Malian adults described in **Section 1.6.3**, CPG 7909 has not been administered to humans in malaria-endemic areas, or in populations with a high burden of infectious disease. It is possible that the safety profile and immunologic response to CPG 7909 may be different in these populations.

Animal studies have found serious, unexpected fetal and maternal problems when CPG 7909 was given to pregnant rats and rabbits. These studies used a dose of CPG 7909 more than 100 times higher than the dose used in this study. These problems included decreased maternal and fetal weight gain as well as a variety of malformations of the fetal skeleton and organs. For this reason, women who are pregnant or who may become pregnant will not be enrolled in the study. Women who participate in the study must use a reliable method of birth control before the start of the study and for at least 3 months after receiving the final vaccination. Pregnancy testing will be completed on female subjects multiple times during the trial. Any female participant interested in contraceptive methods will be referred to the local health center family planning services for evaluation and institution of an appropriate contraceptive method.

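### Fatigue and chills are named as possible reactions but not solicited, and fatigue is graded by a different Grade 2 rule from malaise, under a heading for unexpected events

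*Protocol*

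**What the plan says.** The Immunization risk section (12.5.2 in the contents, printed as 12.1.2) states: "Systemic reactions such as fever, chills, headache, fatigue, malaise, myalgia, and joint pain may also possibly occur". For CPG 7909 as an adjuvant it reports a moderately raised incidence of "mild to moderate local and systemic AEs after vaccination (injection site pain, myalgia, fatigue", with fatigue the last item in that bracket. The section on previous experience with CPG 7909 says of the influenza vaccine trial: "The most frequently reported adverse events were injection site pain, headache, myalgia, and fatigue".

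Under the label "Solicited Adverse Event", Appendix C lists fever, headache, nausea, malaise, myalgia, arthralgia and urticaria. Fatigue and chills are absent. Fatigue has a row in the Systemic table of Appendix E, which is introduced by "These tables are to be used to grade unexpected adverse events not described in Appendixes C and D". Chills has no row in either appendix and so falls to the default scale under Determination of Severity.

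The primary endpoint is the incidence and severity of systemic and local adverse events. Section 11.1.1 plans "A line listing of each clinical and laboratory AE classified as local, solicited, or other", a summary by severity, a comparison of the proportion with at least one event, and a sign test on each subject's event counts in the two weeks after each vaccination.

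**The concern.** Reactogenicity is the primary objective. Symptoms asked for by name are usually recorded more completely than those left to general questioning, so the solicited list should cover what the protocol itself anticipates. It omits a symptom that the protocol links to the adjuvant, and no reason is given.

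Severity is part of the primary endpoint. If fatigue and malaise follow different rules, the grade a participant receives depends on the word that goes on the form. The heading of Appendix E also applies a term defined elsewhere in the protocol to a reaction that the risk section anticipates.

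Mali has most to gain from a correction. It is the randomised, blinded part of the trial, it has no symptom diary, and its post-dose visits specify a history and a focused examination without a symptom list.

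**Working it through.** **1. Risk section against the appendices.**

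| Systemic reaction named in the risk section | Appendix C | Appendix E |
|---|---|---|
| Fever | yes | no |
| Chills | no | no |
| Headache | yes | no |
| Fatigue | no | yes |
| Malaise | yes | no |
| Myalgia | yes | no |
| Joint pain | yes (arthralgia) | no |

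Seven are named and five are solicited, so 7 − 5 = 2 are not: fatigue and chills. The risk section lists malaise and fatigue separately, so the protocol does not treat them as one term.

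**2. Grading the same complaint.** Take a participant who takes a tablet for the complaint but keeps up normal activity.

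- Written as malaise: Appendix C makes it Grade 2, because that row reads "Malaise that interferes with daily activity, or treatment given" and the treatment clause alone is enough.
- Written as fatigue: Appendix E makes it Grade 1, because the grade depends only on interference with activity.
- Written as chills: the default scale makes it Grade 2, because that scale also counts treatment given.

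Fatigue is the exception among the three. The difference is one grade, at the Grade 1/Grade 2 boundary. At Grade 3 the fatigue row reads "Significant, prevents daily activity", and the malaise row also turns on daily activity being prevented, so the tables agree there.

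**3. Which outputs are touched.** The primary endpoint, the overall frequency summary and the any-event comparison cover all adverse events, so fatigue and chills count in each. The severity summary inherits the Grade 1/Grade 2 difference. In the line listing both symptoms fall under other, so a table restricted to solicited events would omit them. The halting rule refers to related Grade 3 systemic events whatever table graded them, and is unaffected.

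**4. The protocol's own figure.** The sample-size section gives 0.80 as the probability of seeing at least one event with n = 12 and p = 0.125. The formula is P = 1 − (1 − p)^n. With these inputs, 1 − 0.875^12 = 0.7986, which reproduces it. With all 15 enrolled, P = 0.865.

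If only a fraction c of affected subjects had the symptom recorded, then P = 1 − (1 − 0.125c)^n:

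| Assumed c | n = 12 | n = 15 |
|---|---|---|
| 1.0 | 0.799 | 0.865 |
| 0.9 | 0.761 | 0.833 |
| 0.75 | 0.693 | 0.772 |
| 0.5 | 0.539 | 0.620 |

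The values of c are assumptions. The protocol gives no capture fraction, and nothing in it shows that c is below 1.

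**5. Whether the US prompts can change.** All 30 US volunteers had been enrolled by 30 September 2009, and the protocol reports events after first or second vaccination. A prompt added only for third doses could raise recorded counts after dose 3 relative to dose 1. The sign test compares exactly those counts within subject, so the prompt would bias it. In Mali the prompt can apply to every dose in both arms if it is in place before the first vaccination.

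**The case against.** A reader might infer that the primary reactogenicity rates will under-count fatigue and chills. The documents do not support that. The endpoint and the any-event comparison are not limited to solicited events. Adverse events are elicited by questioning and examination at each contact, all systemic reactions go on the case report form, and the US diary is open to any systemic symptom. Mali has visits on Days 1, 2, 3, 7 and 14 after each dose, and the US systemic events that reached Grade 3 typically occurred within 24 hours. The diary and the Mali forms are not shown, so it is not established that malaise is prompted by name while fatigue is not.

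A reader might also put a power loss on a fatigue comparison in Mali. With assumed true rates of 60% and 10% and 15 per arm, a two-sided 5% Fisher exact test has 74% power at full capture and 28% at half capture. The arithmetic is right, but the rates and capture fractions have no source in the protocol, and no fatigue-specific test is planned in a trial that calls itself exploratory.

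The evidence for expectedness also has limits. Chills is given only as a possible vaccine reaction and is never tied to CPG 7909. The influenza trial statement covers arms with and without the adjuvant. Formal unexpectedness rests on the Investigator's Brochure or package insert, as determined by the sponsor, so the Appendix E heading alone does not show that fatigue would be misreported.

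All of this limits the consequence. It does not remove the mismatch between the risk section and Appendix C, the differing Grade 2 rules or the loose heading.

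**Conclusion.** The point holds as a gap in how part of the primary safety endpoint is measured. It does not show that the primary rates are wrong. Three things follow from the text without assumptions: two of seven named systemic reactions are not on the solicited list; a treated, non-limiting complaint differs by one grade between malaise and fatigue; and Appendix E labels as unexpected a reaction that the risk section anticipates.

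Less complete recording of the two symptoms is possible. Its size cannot be derived from the document, and the capture table above is illustration only. The any-event comparison still counts every recorded event, and the halting rule does not depend on the solicited list. This is a low-cost improvement and worth making.

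**What to change.** - Add fatigue and chills to Appendix C with the grading form used for malaise and myalgia, including the treatment clause at Grade 2.
- Ask for both by name in both arms at the Mali post-dose visits, from the first dose. This assumes Mali vaccination has not begun. The protocol supports that: it reports only US vaccinations and says the vaccine has not been tested in malaria-exposed people.
- Remove fatigue from Appendix E and drop the word unexpected from its heading.
- In the US, leave the diary prompts unchanged so that the between-vaccination sign test is not biased. Tabulate fatigue together with malaise, and state which grading rule applied to fatigue already recorded.

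The cost is two table rows, one heading and a prompt on the Mali form, with no extra visit. The downside is that rates of these two terms will not be directly comparable between sites and need a footnote. The planned group comparisons are within site and are not affected.
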